## Abstract

**Background:**

Due to the growing number of elderly with advanced chronic conditions, healthcare services will come under increasing pressure. Teleconsultation is an innovative approach to deliver quality of care for palliative patients at home. Quantitative studies assessing the effect of teleconsultation on clinical outcomes are scarce. The aim of this present study is to investigate the effectiveness of teleconsultation in complex palliative homecare.

**Methods/Design:**

During a 2-year recruitment period, GPs are invited to participate in this cluster randomized controlled trial. When a GP refers an eligible patient for the study, the GP is randomized to the intervention group or the control group. Patients in the intervention group have a weekly teleconsultation with a nurse practitioner and/or a physician of the palliative consultation team. The nurse practitioner, in cooperation with the palliative care specialist of the palliative consultation team, advises the GP on treatment policy of the patient. The primary outcome of patient symptom burden is assessed at baseline and weekly using the Edmonton Symptom Assessment Scale (ESAS) and at baseline and every four weeks using the Hospital Anxiety and Depression Scale (HADS). Secondary outcomes are self-perceived burden from informal care (EDIZ), patient experienced continuity of medical care (NCQ), patient and caregiver satisfaction with the teleconsultation (PSQ), the experienced problems and needs in palliative care (PNPC-sv) and the number of hospital admissions.

**Discussion:**

This is one of the first randomized controlled trials in palliative telecare. Our data will verify whether telemedicine positively affects palliative homecare.

**Trial registration:**

The Netherlands National Trial Register NTR2817

## Background

Palliative care has become an important public health issue since the past decade [1]. The ageing of the population and the rising life expectancy are contributing to this development. Also, the pattern of diseases people suffer and die from has changed from acute illnesses towards chronic illnesses [1-3]. In addition to advances in medical knowledge and technology that increase treatment possibilities at the end of life, these epidemiological transitions have led to a growing need of palliative care in the last phase of life [4].

The primary goal of palliative care is to ensure the best possible quality of life of patients and their families facing a life threatening illness [1,5]. Most people in their end-stage of life, regardless of their initial disease, want to be cared for and to die at home [6,7]. Therefore, place of death is considered an indicator of quality of end-of-life care [8]. However, research in Belgium and in the Netherlands has shown that 30-40% of palliative patients are transferred from home to a hospital or health care institution in the last week of life [9,10]. This trend is also seen internationally [11]. Transitions in the location of care are often extremely stressful for patient and caregivers [11] and can pose a challenge for the continuity of care [11,12].

Place of death has also become a topic of wider interest for public health policy, due to the focus in health care on cutting costs in acute care settings [13]. Many European countries have implemented policy measures to reduce the number of acute care hospital beds as a means to restrict hospital expenditure [5]. With this shift in location of care for the seriously ill from hospital to home, the reliance on family caregivers to support patients with terminal illness at home is growing [13]. These family caregivers are of vital importance for those wanting to die at home. Without them, remaining at home in the last phase of life would be impossible for many patients [14,15]. However, caregiving for terminally ill patients can be burdensome for informal caregivers, possibly leading to burn-out [16,17].

Due to a growing number of palliative patients and the desire for less institutionalized care, community-based palliative care will become a big challenge [18]. The development of innovative approaches to deliver good quality of care at home is therefore necessary. One such approach is the use of telemedicine. Telemedicine is the use of telecommunications and information technologies to share and maintain patient health information and to provide clinical care and health education to patients and professionals when distance separates the patients [19]. Teledermatologic consultation has been one of the first applications of telemedicine. Literature shows that this form of teleconsultation reduces the number of traditional face-to-face consultations with a dermatologist [20-23]. In addition, a telemedicine approach has also been proven cost-effective in diabetes care and pediatrics [24,25]. In the field of palliative homecare however, few quantitative studies have been carried out [26-30]. These studies often are of moderate methodological quality. Common shortcomings are small sample sizes, comparability of intervention and control groups and the handling of drop-outs [26,31].

Teleconsultation is a specialized form of telemedicine that uses technology to provide real-time visual and audio patient assessment [32]. Teleconsultation is an instrument to bring across expertise from the hospital into primary healthcare and can therefore be very useful in complex homecare for palliative patients and their families. This study aims to evaluate the effectiveness of teleconsultation in palliative homecare. The primary goal is to evaluate the effectiveness of teleconsultation on the symptom burden of palliative patients at home. Secondary objectives are 1) to investigate whether teleconsultation influences the number of hospital admissions by acting more pro-active on escalating problems of patients, 2) to consider if the burden of the family caregiver changes by giving them a better opportunity to address their needs and problems, 3) to study the patient experienced continuity of medical care in the last phase of life, 4) to assess patient and caregiver satisfaction with the teleconsultation contact and 5) to investigate patient's problems and needs for palliative care.

The objective of this report is to present the protocol of the study used for data collection in 2011 and 2012.

## Methods/Design

### Study design

The study consists of a two-armed cluster randomized controlled trial. To prevent possible bias at the level of GPs, a clustering will take place on the level of the GP. The symptom burden of the patient and the secondary outcomes in the two study arms will be compared.

Parallel to this cluster randomized controlled trial, a qualitative study will be undertaken. In this qualitative study, semistructured interviews and observations will be used to consider the socio-ethical aspects of teleconsultations in palliative homecare. The findings from the quantitative and the qualitative study will be integrated in future articles.

### Randomization

Participating GPs will be randomly assigned to the intervention group or to the control group. Due to clustering of GPs, all subsequently referred patients will be in the same study group. A block design with different length of blocks (4 and 6) will be used to give an equal balance between groups. An independent researcher will generate and store the randomization code.

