### Study population

On the moment of inclusion, the patient's GP acts as the coordinator of medical care, and patients reside at their homes. Besides the place of residence, the inclusion criteria are:

- Dutch-speaking patients, aged 18 years or older, with a progressive oncological disease,

- a score of ≤ 60 on the Karnofsky Performance Scale (assessed by the GP),

- a life expectancy of ≤ 3 months.

Patients unable to give informed consent and patients with an active psychotic disorder or a serious cognitive disorder are not eligible for inclusion.

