### Recruitment, consent and data collection

For the purpose of this study, all GPs practicing in the Nijmegen region are invited with a letter, in which the aim and procedure of the study are clarified. Furthermore, the advantages and disadvantages of participating are mentioned and contact information for advice from an independent physician is given. The researcher contacts the GPs several days after receipt of the letter. When more information is needed, the researcher visits the GP to inform him/her more extensively about the trial. When a GP refuses to participate, the researcher will document the arguments for non-respondent analysis. Inclusion starts at April 1 2011 and runs to October 1 2012.

When the patient and the family caregiver decide to join the study, they sign the informed consent form during a one-hour home visit by the researcher. After informed consent, the patient and the family caregiver will first complete the baseline measurement. The baseline measurement consists of several demographic questions and four short questionnaires for the patient. The four questionnaires (ESAS, PNPC-sv, HADS and NCQ) will be completed at home every four weeks during the study participation. The ESAS will be completed every week, as symptom burden is our primary outcome. The family caregiver completes a questionnaire on self-perceived pressure from informal care (EDIZ) at baseline and every two weeks. At time points where there is no home visit, the ESAS and EDIZ will be returned in a stamped envelope. The family caregiver receives a mobile phone text message as a reminder to fill in and post the questionnaires. The flowchart of the inclusion is described in Figure 1.

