### Sample size calculation

The null hypothesis of this cluster randomized trial is that there are no significant differences in symptom distress between palliative patients at home with and without a telemedicine-computer for videoconference. Symptom distress will be measured by the Edmonton Symptom Assessment Scale (ESAS). The ESAS is a 0 to 10 numeric scale (0 = best, 10 = worst) to rate severity of 10 symptoms. The sum of all 10 scales makes the Total Distress score (max.100). Based on a study of Follwell et al. [43] we determined a Total Distress score of 8 as the minimum clinically important difference for the power calculation. Without a cluster-effect and without repeated measures, we would need 80 patients per condition, assuming an α of .05 and a power of 80% (calculated with nQuery advisor 4.0). However, there is a cluster-effect and there are repeated measures that we corrected for.

To correct for clustering, we multiplied the abovementioned sample size with the design factor (1+(n-1)ICC), where n is the number of patients and ICC the intra cluster correlation. Assuming 3 enrolled patients per GP and an ICC of 0,1 (based on Knox & Chondros [44]), the design factor for clustering is 1,2.

To correct for repeated measures and baseline measurement, we also multiplied the sample size with the design factor ((1+(k-1)ρ)/k- ρ_0_^2^). In this formula, k is the number of repeated measures, ρ is the (mean) correlation between pairs of post-tests and ρ_0 _is the (mean) correlation between a post-test and the baseline measurement. Here, k = 13, and we state ρ = 0,45 [34] and ρ_0 _= 0,35. The design factor for repeated measures is therefore 0,37.

That makes the total required sample size 80 × 1,2 × 0,37 = 36 patients per condition. Taking into account an early drop-out of patients, we aim to include 50 patients per condition. This calculation is based on Follwell et al. [43], who considered a drop-out of 30% within an inclusion period of 1 month. Because the inclusion period in our study is longer (estimated life-expectancy of approximately 3 months at inclusion), we chose a higher drop-out percentage (39%).

Put briefly, a sample size of 100 patients (α = .05, power = 80%) is required to detect differences in change of symptom distress between the intervention group and the control group.

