## Discussion

This study investigates the effectiveness of teleconsultation in complex palliative homecare. It compares clinical outcomes in the intervention group with a control group. The intervention consists of a weekly teleconsultation with the palliative consultation team. Bringing specialist expertise to the home via video-telephone technology is an innovative way of improving complex homecare for palliative patients. A strength of our study is the robust design. We plan to conduct a cluster randomized controlled trial, which will be one of the first in palliative homecare, at least in the field of telemedicine. Furthermore, symptom burden is our primary outcome measure. Studies with clinical outcome measures are scarce in research on palliative homecare. Therefore, future data on this primary outcome measure, when positive, will be very helpful in the adoption and implementation of telemedicine services in palliative care.

However, there are also several challenges in this study. A first challenge will be to enroll a sufficiently large sample to make sure that differences between the intervention group and the control group can be detected. If recruitment problems occur, the palliative consultation team and the regional home care organization will additionally be involved. Finally, this research project stimulates collaboration between primary care and hospital care in order to optimize the continuity of care. Besides this process innovation, we also focus on technical/product innovation. In a world where technology is changing rapidly, it is a big challenge to carry out innovative research.

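### After each GP's first referral, patients are chosen by a GP who already knows the arm; at the planned cluster size that is about two thirds of the sample

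*Protocol article*

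**What the plan says.** The Methods/Design part of the Abstract gives the trigger for randomisation: "When a GP refers an eligible patient for the study, the GP is randomized to the intervention group or the control group". The Randomization section fixes what follows: "Due to clustering of GPs, all subsequently referred patients will be in the same study group". On concealment it says "An independent researcher will generate and store the randomization code", with blocks of 4 and 6.

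The Study population section lists among the entry criteria "a score of ≤ 60 on the Karnofsky Performance Scale (assessed by the GP"). Under Intervention, the palliative consultation team advises the GP on treatment after the first teleconsultation, so a GP in that arm cannot be unaware of it.

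Under Recruitment, consent and data collection, consent is signed at a home visit by the researcher, and "After informed consent, the patient and the family caregiver will first complete the baseline measurement". That section does not say where randomisation falls in the sequence.

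The Sample size calculation plans cluster size and total as "Assuming 3 enrolled patients per GP and an ICC of 0,1" and "we aim to include 50 patients per condition". The Study design section presents clustering as a way to prevent bias at GP level. The Multivariate analysis section names linear mixed models, on the ground that the design has a pretest, repeated measures and clustering.

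**The concern.** Randomising GPs protects the comparison of patients only if the patients are identified before the arm is known, or by someone who does not know it. Here that holds for the selection of each GP's first patient and for nobody after that. The independently held code hides a GP's own assignment until it is made. It cannot hide an arm that the GP has already been told.

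There is a plausible motive to refer differently. In one arm the patient gets a free home computer and weekly specialist contact, and the GP gets advice. In the other arm neither the patient nor the GP gains anything comparable. An intervention GP may refer the more complex patients, and a control GP may refer fewer or different ones. The arms could then differ in severity or prognosis for reasons that randomisation does not balance, and more patients would not cure it. The direction cannot be predicted, so an effect could be hidden as easily as created.

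Clustering answers a different problem, namely contamination when one GP treats patients in both arms. It also creates this route to bias. No section of the article describes a safeguard.

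**Working it through.** **Inputs from the Sample size calculation.** 3 patients per GP; ICC 0.1; 50 patients per arm (100 in total); target difference 8 points on the ESAS Total Distress score; k = 13 repeated measures; correlation between post-tests 0.45; correlation of a post-test with baseline 0.35; 80 patients per arm before correction.

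**The plan's own figure.** The cluster factor is 1 + (3 − 1) × 0.1 = 1.2. The repeated-measures factor is (1 + 12 × 0.45)/13 − 0.35² = 0.4923 − 0.1225 = 0.3698. Then 80 × 1.2 × 0.3698 = 35.5, which rounds up to the stated 36 per arm. The inputs are therefore read as the plan uses them.

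**Share of patients referred with the arm known.** With a mean of m patients per enrolling GP there are 100/m first patients, so the share that comes later is (m − 1)/m. This depends only on the mean, not on how cluster sizes vary.

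| Mean patients per GP | First patients of 100 | Later patients of 100 |
|---|---|---|
| 1.5 | 67 | 33 |
| 2 | 50 | 50 |
| 3 (planned) | 33 | 67 |
| 4 | 25 | 75 |
| 5 | 20 | 80 |

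Only the row for 3 rests on the plan; the others show the range.

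**Illustration of size.** Let b be the difference between arms in mean underlying ESAS among later patients that is due to selective referral. The documents give no value, so b is assumed. First patients are taken as balanced.

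- Raw arm difference = (2/3) × b.
- Adjustment for baseline as a covariate, with equal variances at baseline and follow-up, has slope 0.35. The residual is (2/3) × b × (1 − 0.35).

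| Assumed b | Raw difference | Residual after adjustment | Residual as share of 8 |
|---|---|---|---|
| 3 | 2.0 | 1.3 | 16% |
| 5 | 3.3 | 2.2 | 27% |
| 8 | 5.3 | 3.5 | 43% |

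If GPs average 2 patients, b = 5 gives 5 × 0.5 = 2.5 raw and 2.5 × 0.65 = 1.6 after adjustment.

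**Dependence on the model.** The covariance-type adjustment matches the subtraction of the squared baseline correlation in the plan's sample-size factor. The same section, however, ends by speaking of differences in change, and the Multivariate analysis section does not fix how the pretest enters. In an analysis of change, a level shift that stays constant over time cancels and the residual is about 0. Selection on prognosis or trajectory would not cancel, and the documents give nothing from which to size it.

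**The case against.** **No evidence of bias, and an invented size.** The documents show an open route, not that any GP would use it. The 5-point shift is an assumption without direction, and the 2.2-point residual belongs to one model. This stands, so the firm part of the point is the share of patients exposed, not the points of bias. The word *most* also depends on the planned 3 per GP and fails at 2 or fewer.

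**The first patient is protected.** Randomising at referral means that each GP selects the first patient before knowing the arm. That is a real strength. A reader might still infer that the first patient consents and completes baseline after allocation. The Abstract read with the recruitment section suggests that order, but neither states it. The inclusion flowchart (Figure 1), which may settle it, was not available to me. Nor does the text say that the patient is told the arm before baseline.

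**Two further inferences go too far.** A reader might conclude that the GP, knowing the arm, also judges life expectancy. The Study population section names the GP as assessor only for the Karnofsky score. A reader might also conclude that the team delivering the intervention would pick patients if recruitment lags. The Discussion says only "If recruitment problems occur, the palliative consultation team and the regional home care organization will additionally be involved"; it does not say that the team would select or refer anyone.

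**Analysis detail belongs elsewhere.** Covariates and sensitivity analyses are commonly left to the analysis plan, and their absence from the article is no fault. The fault lies in the stated order of randomisation and referral; the analyses are offered as remedies for it.

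**Conclusion.** The point holds for later patients. The stated design has every patient after a GP's first identified, and rated on one entry criterion, by a GP who knows the arm. At the planned 3 patients per GP that is about 67 of 100 patients, or half if GPs average 2. Neither clustering nor the stored code guards against this, and the pretest does so only partly.

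The size of any bias is unknown. For assumed shifts of 3 to 8 points among later patients, the residual is 1.3 to 3.5 ESAS points under covariance-type adjustment with correlation 0.35 and equal variances. It is near 0 for a constant level shift in a change analysis. For the first patient, allocation before consent and baseline is suggested but not stated, so that is a matter to clarify rather than an established defect.

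**What to change.** 1. State that a GP is randomised only after the first patient has consented and completed baseline. If this is already the practice, only the wording changes.
2. For later patients, do not disclose the arm to the patient until baseline is complete. This protects consent and self-reported baseline scores, as far as the GP cooperates.
3. Adjust the primary model for baseline ESAS and for the Karnofsky score already obtained at entry. For later patients that score is itself given by a GP who knows the arm, so it helps only in part.
4. Prespecify a sensitivity analysis restricted to each GP's first patient, the group whose selection is free of this problem.
5. Report the number of referrals and the baseline characteristics of later patients by arm, so that readers can see any selection.

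The cost is a change in the order of steps and a little extra analysis. The arm becomes known a few days later for the first patient. The first-patient analysis would rest on about 33 patients and be imprecise, so it is a check and not a replacement. Together these steps reduce selective referral and make it visible, but they do not eliminate it while the GP who refers is unblinded.

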### Study population

On the moment of inclusion, the patient's GP acts as the coordinator of medical care, and patients reside at their homes. Besides the place of residence, the inclusion criteria are:

- Dutch-speaking patients, aged 18 years or older, with a progressive oncological disease,

- a score of ≤ 60 on the Karnofsky Performance Scale (assessed by the GP),

- a life expectancy of ≤ 3 months.

Patients unable to give informed consent and patients with an active psychotic disorder or a serious cognitive disorder are not eligible for inclusion.

### Intervention

After completing the baseline measurement, a telemedicine computer will be installed at the patient's home. Soon after the installation, the nurse practitioner of the consultation team contacts the patient to make an appointment for the first teleconsultation. During this first digital screen-to-screen contact between the patient and the nurse practitioner, the nurse checks for problems in palliative care following a predefined consultation protocol (e.g. physical problems, social problems, coordination of care). After the first teleconsultation, the nurse practitioner, in cooperation with the palliative care specialist of the palliative consultation team, advises the GP on the treatment policy for the patient. During this trajectory, the GP continues to be the coordinator of medical care. The teleconsultations will return every week, but more frequent contact is possible when the patient and the team desire this. There are no installation or internet costs for the patient and also the use of the telemedicine computer is for free.

The telemedicine application is a computer with a touch screen, a microphone/speaker and a camera. Large and easy to understand pictograms make the program user-friendly. To contact a nurse or a physician for a videoconference, the patient just has to touch the image of that person. In addition to the weekly teleconsultations, the patient also has the opportunity to videophone the 24/7 support service of the homecare organization. Furthermore, an information database, an internet-browser and some entertainment options are available on the telemedicine application. The telemedicine application will not be used in emergency situations due to safety restrictions.

